#### *9.2.3 Joint intervention for both the active and control group:*

All participating patients receive a book on general stress management ("Stress, Lgens Bord" Netterstrm, Bo, DR, 2002).

### **9.3 Blood sampling and analysis:**

Blood samples are taken locally at Herlev Hospital where they are stored at -80 degrees until analysis.

After analysis, and by June 1st 2013, the debris is destroyed.

All blood tests will be performed at Medical Department O, Endocrinology Unit, Research Lab 5404, Herlev Hospital, either as a routine or as a research analysis through commercial analysis-kits. All samples are analyzed in the same assay to avoid inter-assay variation, i.e. the analyses are first performed after completion of the study.

The following is analyzed (baseline study and intervention study combined):

Measure of persistent stress: HbA1c, serum Oxytocin.

Measure of insulin resistance: Fasting serum / plasma insulin, C-peptide, blood glucose (with calculation of HOMA), HbA1c, Adiponectin.

Measure of chronic inflammation: Serum / plasma high sensitive CRP, Defensin, YKL-40.

Measure of fat metabolism: total cholesterol, HDL and LDL cholesterol and Triglycerides.

Measure of cardiac strain: NT-proBNP and BNP.

Besides this, a spare glass of 5 ml of blood is taken for any later use at baseline and

at the 3 month follow-up. These spare glasses are stored in coded form (without CPR number) in one of the Danish Data Protection Agency and the Capital Region's approved bio banks (database id: 30122009.HEH.O.JF). This database is an ongoing database without a planned end date.

#### **9.4 Body composition:**

The body composition is done using whole-body DEXA scan (apparatus: Hologic) for the determination of body composition in fat, muscle and bone mass.

Furthermore, the visceral

fat is calculated using new software to distinguish between android and gynoid fat. A well-calibrated x-ray is used for the scanning of the patient.

#### **9.5 HRV post test:**

The subjects get their short-term HRV (5 minutes) measured by an EKG (heart electro diagram) in supine rest. The measurement is done with the participant lying on a folding bed. After the rest, the participant is tilted without using his or her own muscle power to a 70 degrees (upright) position. EKG is registered in this position. The difference between resting and standing represents the reactivity of the autonomic nervous system. Lower reactivity in the autonomic nervous system is associated with persistent stress. The measurement of HRV is non-invasive and is not associated with discomfort or any risk for the participants.

#### **9.6 Algometry on the Tibia bone with an established Algometer**

Pain threshold will be measured at the Tibia bone with both the PPS measure device used in this study as well as with a known and established algometer (Arndt-Nielsen et al. 2010). Fifty randomly selected patients will be studied during their follow-up visit after 3 months.

### **10. Time frame for the study**

- The first patient is expected to begin 3 months after the financial resources has been provided, and after approval by the Scientific Ethics Committee and the Danish Data Protection Agency.

- The inclusion period ends when the desired number of included patients is reached (300).
- The treatment period ends three months after the last patient is included.
- The scientific main article is expected to be complete after 3 additional months.
- The total project period is estimated as one year from the inclusion of the first patient.

## 11. Statistics

### 11.1 Power and calculation of the size of the study population

The primary analysis is based on the depression score of the MDI questionnaire. The prevalence of depression measured as a MDI score  $\geq 20$  was found to be approximately 20 % in patients with ischemic heart disease (Olsen et al 2003; Bech P 2001). In a study with 292 office workers, the prevalence of a MDI score  $\geq 20$  was twice as high in people with a PPS measure  $\geq 60$  compared to people with PPS  $< 40$  (Ballegaard et al 2011). Against this background, it is estimated that among patients with ischemic heart disease who at the same time have an elevated PPS measure the prevalence of an MDI  $\geq 20$  is increased by 80 % compared to patients with ischemic heart disease as a whole, i.e. 36 %.

The Minimal Important Difference (MID) is set at 0.4 when the effect of active treatment is compared to control treatment. MID in terms of improvement of a MDI score is set at 5 points on the MDI scale when the active and control groups are compared. The standard deviation of improvement in both groups is set at 9 units on the MDI scale. Alfa is set at 5 %, Beta at 20 %. Against this background, 50 patients with an MDI score  $\geq 20$  are required in each group, thus 300 patients in total when safety margins of 10 % of the estimated values are included.

An interim analysis on the first 60 patients included showed, that the anticipated prevalences for MDI score were different than found. Therefore the cutpoint on the MDI scale was changed to MDI score = 15.

- Effect size is calculated from all included patients (on intention to treat basis)
- Effect size is a fraction that consists of the difference in a MDI score from before intervention till after treatment for the active group, minus the same

difference for the control group divided by the spread of the change in MDI score, when taking all patients together. In a review of all of the 12 SSRI preparations that the FDA has approved for treatment of depression, the average effect size is 0.3 (Turner et al., 2008). Example: the MDI score in active group changes from 24 to 11 ( $24-11 = 13$ ); while the MDI score for the control group changes from 24 to 14 ( $24-14 = 10$ ). This change in the MDI score is  $13-10 = 3$ ; if the spread (standard deviation) on the MDI score overall are 7.5, the effect size will be  $3/7.5 = 0,4$  ([name], 2010).

- The Minimal Important Difference (MID) in effect size for the WHO-5 questionnaire is calculated similarly to 0,5 ([name], 2010).

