### **Ad 3: The PPS measurement's specificity and sensitivity**

When the discrimination criteria mentioned above are used for a two-parted categorization regarding grouping from a PPS measurement that is 60 units, the specificity was 0.79 and the sensitivity 0.32 was found in terms of the prevalence of clinical stress signs, mental and physical health measured by the SF-36 and the prevalence of depression measured by the MDI. The result is deemed acceptable since the high specificity ensures that a large percentage of the people not in need of treatment are not offered. The low sensitivity can cause some people to be offered treatment even though the need is not present, but since the treatment is harmless and without side-effects, it is deemed acceptable.

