## **7. Practical course (including flowchart)**

Using databases of cardiac rehabilitation patients from Gentofte and Herlev Hospital respectively approximately 600 patients with complete cardiac rehabilitation course > 6 months ago, to ensure a steady state in regard to the efficacy of the given cardiac rehabilitation, are identified. The patients are invited by letter to participate in the study.

It is expected that about 450 will accept. These are convened to an examination at Herlev Hospital Medical Department O.

All patients sign the consent form and go through the physiological preliminary examination.

Patients with PPS < 60 are ended immediately, and a subset of the first 50 patients with PPS < 45 are invited to a measuring of their body composition.

Since it is expected that 2/3 of patients have an elevated PPS measure ( $\geq 60$ ), 300 patients with PPS  $\geq 60$  are randomized to either an active or control group with 150 in each:

**Control group:** Continue their own efforts in extension of the already given cardiac rehabilitation and receive a textbook on general stress management (REHAB + CARE).

**Active group:** the same plus the Ull treatment program (REHAB + ULL).

All included patients will at baseline be offered an additional measurement of body composition.

Intervention period: 3 months.

Both the control and active group continue with the given medical treatment. If there is a change in heart condition including possible side effects of medication, the medication is adjusted according to the procedures in the rehabilitation programs at the hospital the patient is assigned to (Gentofte or Herlev Hospital). If possible, the medication should remain stable during the 3 months of the observation. The patient and the patient's own doctor are informed that the aim of the study is that any adjustment of cardiovascular medicine happen after contact with the project nurse (perhaps through a telephone hot-line).

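### The 36% prevalence of MDI ≥20 behind the sample size of 300 exceeds the 30% ceiling set by the protocol's own planning figures, and power was not restated when the cut-point moved to 15

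*Protocol*

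**What the plan says.** Protocol section 11.1 bases the sample size on patients with an MDI score of 20 or more. It says that this prevalence "was found to be approximately 20 % in patients with ischemic heart disease". It then assumes that in patients with ischemic heart disease and raised PPS the figure "is increased by 80 % compared to patients with ischemic heart disease as a whole, i.e. 36" per cent. The support offered is a twofold ratio among office workers, comparing PPS ≥60 with PPS <40.

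With a difference of 5 MDI points, SD 9, alpha 5% and beta 20%, the section asks for 50 patients with MDI ≥20 in each group and arrives at 300 in total, including a 10% margin on the estimates.

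Section 7 plans recruitment separately: "It is expected that about 450 will accept", and "it is expected that 2/3 of patients have an elevated PPS measure", which gives the 300 with PPS ≥60.

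Section 11.1 adds that an interim look at the first 60 patients found prevalences other than those anticipated: "Therefore the cutpoint on the MDI scale was changed to MDI score = 15". The minimization in section 8 uses 15. The same section 11.1 calculates the effect size from all included patients, section 11.2 includes all enrolled patients, and section 12 judges success at an effect size of 0.4 with no restriction by baseline MDI.

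**The concern.** The prevalence in a subgroup cannot be so high that the subgroup alone holds more cases than the whole population. The larger the subgroup, the tighter that limit. Here the subgroup is expected to be two thirds of those examined, so its prevalence can be at most 1.5 times the overall figure, yet section 11.1 uses 1.8 times. The cited twofold ratio does not support 1.8 either, because its comparator is PPS <40 and not patients as a whole.

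The 36% is the only link between the 50 per group and the 300. If it is wrong, the stated 80% power for the MDI ≥20 stratum is wrong as well. The change of cut-point concedes that the prevalence assumption failed, but the text gives no prevalence of MDI ≥15, no new expected number and no new power. A reader cannot tell which population the trial is powered for, or for what difference.

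**Working it through.** **Inputs.** Section 11.1: overall prevalence of MDI ≥20 about 20%; assumed prevalence with raised PPS 36%; difference 5; SD 9; alpha 5%; beta 20%; 10% margin. Section 7: about 450 examined, two thirds with PPS ≥60, 150 per group. The sidedness of alpha is not stated; two-sided reproduces the plan's figure (one-sided gives 41 per group).

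**Step 1: reproduce the plan.**
- n per group = 2 × [9 × (1.960 + 0.842)/5]² = 50.9, so 51 (52 by the t-test). The stated 50 is reproduced within rounding.
- Total: 100/0.36 = 278. With a 10% margin, 278 × 1.1 = 306 or 278/0.9 = 309. The stated 300 is within 3%.

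So 300 does come from the 36%.

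**Step 2: test the 36%.**
- Overall prevalence ≥ P(MDI ≥20 | PPS ≥60) × P(PPS ≥60).
- At 36%: 0.36 × 2/3 = 24%, above the stated 20%.
- Ceiling: 0.20/(2/3) = 30%, reached only if nobody with PPS <60 has MDI ≥20.
- The 10% margin does not close the gap: 0.36 × 0.9 = 32.4%, still above 30%.

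**Step 3: what the cited ratio gives.** The ratio of 2 is stated against PPS <40. Assume that it applies against all PPS <60. The low-PPS prevalence is then 0.20/(2 × 2/3 + 1/3) = 12% and the raised-PPS prevalence 24%. The protocol gives no prevalence for PPS 40–59, so this is an assumption.

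**Step 4: expected numbers and power** (two-sided t-test, 5 points, SD 9, before dropout).

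| Prevalence of MDI ≥20 at PPS ≥60 | Expected among 300 | Per group | Power | Patients needed for 100, no margin |
|---|---|---|---|---|
| 36% (plan) | 108 | 54 | 82% | 278 |
| 30% (ceiling) | 90 | 45 | 74% | 334 |
| 24% (step 3) | 72 | 36 | 64% | 417 |

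**Step 5: sensitivity to the inputs.**
- Two thirds elevated, overall 18% to 22%: ceiling 27% to 33%, or 40.5 to 49.5 per group.
- Overall 20%, share elevated 60%: ceiling 33.3%, exactly 50 per group with no margin.
- 36% becomes possible at 20% overall only if at most 0.20/0.36 = 55.6% are elevated, or at two thirds elevated only if the overall figure is at least 24%. Moving both inputs (22% overall, 60% elevated) gives a ceiling of 36.7%. Each of these also needs virtually no one with PPS <60 to score ≥20.

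**Step 6: the population that is analysed.** With all 300 patients, 150 per group, and the section 12 effect size of 0.4 (already in SD units, so no SD is needed), t-test power is about 93% before dropout. Power of 80% is reached at an effect size of about 0.32.

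**The case against.** The strongest reply is that the share with MDI ≥20 does not set the power of the stated primary comparison. Sections 11.1 and 11.2 analyse everyone, section 12 sets no MDI threshold, and 150 per group give about 93% power for 0.4. This stands, and it limits the consequence. A reader might infer that the trial is underpowered for its primary analysis; the documents do not show that. A smaller effect in low scorers could dilute the overall effect, but the protocol gives no figure for this.

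Second, the inputs are approximate: 20% is a cited figure, and two thirds is an expectation among those who accept. It is therefore tempting to call 36% impossible, or to say that 300 patients cannot supply 100 with MDI ≥20, but both go too far. Even at 30%, the chance of 100 or more among 300 is about 12% (about 0.02% at 24%). The supportable statement is that 36% conflicts with the protocol's own planning figures. Section 11.1 itself ties the 36% to the whole heart disease population, so the comparison is a fair one.

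Third, a reader might apply section 1.4.1.2, where "the specificity was 0.79 and the sensitivity 0.32 was found", to get 0.064/(0.064 + 0.168) = 28%. That should not be used. The pair comes from office workers and covers stress signs, SF-36 and MDI together. At 20% prevalence it also implies only 0.064 + 0.168 = 23% with PPS ≥60, against the two thirds expected here.

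Last, the cut-point of 20 has been given up. MDI ≥15 includes at least as many patients, so the powers in the table do not carry over to that stratum. That is true, but the size sentence still states MDI ≥20 and nothing replaces it.

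**Conclusion.** The point holds as an error in the sample size justification. On the protocol's planning figures, the prevalence of MDI ≥20 among randomised patients is at most 30%, not 36%. The expected number is then at most 45 per group instead of the required 50, with power about 74% instead of 80%. If the twofold ratio is taken to apply against all PPS <60, the figures are 24%, 36 per group and about 64%. All are before dropout, and rest on 20% overall, two thirds elevated, a two-sided 5% test, 5 points and SD 9.

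The move to 15 did not repair this: the size sentence and section 8 now use different cut-points, and no prevalence or power is given for MDI ≥15. The calculation is also made for a subgroup while all patients are analysed. The power for MDI ≥15 cannot be worked out from the protocol.

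**What to change.** Keep N at 300 and amend section 11.1:

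1. Mark 36% as the initial assumption, now superseded, and state that it exceeds the 30% bound implied by 20% overall and two thirds with PPS ≥60.
2. Report the prevalences of MDI ≥20 and MDI ≥15 in the first 60 patients, pooled over arms and without using allocation, and the expected numbers out of 300.
3. Make the cut-point in the size sentence agree with section 8.
4. State the power for the population actually analysed: about 93% for effect size 0.4 with 150 per group before dropout, and the figure after the expected dropout.
5. Give the power of the MDI ≥15 stratum separately, over a stated range of SDs of change. These must be labelled as assumptions, because baseline data can supply a prevalence but not an SD of three-month change or a minimal important difference for patients who start at 15 or more.

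The cost is amendment wording and a short recalculation. No patients are added and no analysis changes. The stated power for the MDI ≥20 stratum falls.

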## 11.2 Analysis of the effect variables

Five percent (5 %) will be used as significance level in all statistic tests.

The statistical analysis will look at two groups of cardiac patients separately: 1) those patients for whom all therapeutic approaches have been exhausted and 2) the rest. One joint analysis will be made if it is statistically reasonable. The statistics are compiled on an "intention to treat basis"; meaning that all enrolled patients are included in the subsequent analysis.

In the statistical analysis, subgroup analysis will be made for the patients with the highest PPS values: e.g. all patients with  $PPS \geq 75$ ; or for the highest quartile of PPS values.

"Closed test procedure" will be used to analyze data after 3 and 12 months in terms of the assessment of the treatment effect:

- First priority hypothesis: The Ull Care program improves the degree of depression measured by a MDI depression score, measured after 3 months of intervention.
- Second priority hypothesis: The Ull Care program improves health economic variables, measured after 12 months of intervention.
- Third priority hypothesis: The Ull Care program improves the frequency of clinical events, measured after 12 months of intervention.

Baseline measurements will be co-variant variables in relation to the applied stratification variable: the degree of depression measured by the MDI scale. Data from before and after the intervention will be analyzed separately. Delta values for

the active and control group respectively will be compared to analyze a possible treatment effect. All secondary and tertiary effect variables will be analyzed after the intervention through variance and regression analysis. If the premises for the proposed statistical analysis cannot be met, non-parametric analysis is used. Quality-of-life data will be analyzed to meet the directions of each of the questionnaires. All effect data will be presented a unifying table and primary, secondary and tertiary effect variables will be listed.

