## 12. Success criteria

The result of the study will be concluded as positive, if the following results are reached:

Compared to the control group, the active group obtains a significant improvement in MDI depression score and with a therapeutic effect size of at least 0,4 when the effect in the active group is compared to the control group (see point 11.1 for exact calculation of the effect size).

When compared to the control group, the active group obtains a significant improvement in mean PPS measurement measured by a professional instructor and with a MID of 10 units on the PPS scale.

The patient does not experience any increased risk in connection with the intervention measured as no increase in blood pressure or serum cholesterol after treatment, Both parts are measured as mean values for the two variables in the active group when the baseline values are compared at the end of the treatment period.

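### Section 11.1 gives two incompatible minimal important differences for the MDI (0.4 and 5/9 = 0.56), sizes a subgroup on the larger, and states no power for the all-patient comparison on which section 12 judges success

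*Protocol*

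**What the plan says.** Protocol section 11.1 fixes the planning values for the primary variable, the MDI score:

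- The target as an effect size: "The Minimal Important Difference (MID) is set at 0.4 when the effect of active treatment is compared to control treatment".
- The target in points: "MID in terms of improvement of a MDI score is set at 5 points on the MDI scale".
- The variability: "The standard deviation of improvement in both groups is set at 9 units on the MDI scale".
- The error rates: "Alfa is set at 5 %, Beta at 20" per cent.

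From these it derives 50 patients per group with an MDI score of at least 20, and 300 in total after an assumed 36% prevalence and a 10% margin. It then reports that the MDI cutpoint was moved to 15 after a look at the first 60 patients, and gives no new required number.

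The same section defines effect size as the between-arm difference in MDI change divided by the standard deviation of the change over all patients together. It says this is calculated from everyone included, by intention to treat. An illustration reaches 0.4 from a 3-point difference, "if the spread (standard deviation) on the MDI score overall are 7.5".

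Section 7 randomizes 150 patients to each arm. Section 12 calls the MDI result positive if the improvement is significant and comes "with a therapeutic effect size of at least 0,4 when the effect in the active group is compared to the control group", and refers back to 11.1 for the calculation.

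**The concern.** Two adjoining sentences give the minimal important difference on two scales, and the standard deviation that follows shows that they are different quantities. The sample size rests on one of them and the success rule on the other. The two are also applied to different sets of patients: the sizing counts patients above an MDI cutpoint, while the effect size is calculated in everyone randomized.

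A reader therefore cannot tell what the 80% power refers to, and finds no power at all for the comparison that decides the trial. It also matters that success depends on the observed effect size and not only on significance, because ordinary power does not describe the chance of passing such a rule. Sections 6.3.4 and 7 make the 12-month health-service and clinical-event analyses conditional on the success criteria, so the threshold also decides whether that work is done.

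**Working it through.** **Inputs.** From section 11.1: 5 points, SD 9, alpha 5%, beta 20%, 50 per group, prevalence 36%, margin 10%. From section 7: 150 per arm. From section 12: threshold 0.4. Section 11.2 says "Five percent (5 %) will be used as significance level in all statistic tests" but does not give the number of sides. I assume two-sided, because it reproduces the stated 50; one-sided gives 41.

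**1. The plan's own figure.** With d the difference divided by the SD, n per group = 2(1.960 + 0.842)²/d² = 15.70/d².

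- d = 5/9 = 0.556: 15.70/0.3086 = 50.9, so 51 (52 by t-test). The stated 50 gives 79% power. It reproduces.
- Total: 100/0.36 = 278. Adding 10% gives 278 × 1.1 = 306, or 278/0.9 = 309, against the stated 300. It reproduces within 3%.

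**2. Do the two targets agree?**

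- 5/9 = 0.556. If the SD is taken over both arms together, it is √(81 + 2.5²) = 9.34, and 5/9.34 = 0.535.
- 0.4 × 9 = 3.6 points.
- For 5 points to equal 0.4, the SD would have to be 5/0.4 = 12.5.

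They do not agree.

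**3. The sizing subgroup at 0.4.**

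- Needed for 80% power: 15.70/0.16 = 98.1, so 99 per group (100 by t-test).
- At 50 per group the standard error of the effect size is √(2/50) = 0.20. Power = Φ(0.4/0.20 − 1.96) = Φ(0.04) = 52% (51% by t-test).

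**4. All included patients at 0.4.**

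- At 150 per arm the standard error is √(2/150) = 0.1155. Power for significance = Φ(0.4/0.1155 − 1.96) = Φ(1.50) = 93%.
- If 10% of patients are lost (135 per arm), it is about 91%.

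These are in standardized units, so they do not depend on the SD being 9.

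**5. The section 12 rule.** At 150 per arm an effect is significant once the observed effect size exceeds 1.96 × 0.1155 = 0.226. The 0.4 threshold lies above that, so it alone decides the MDI criterion. The probability of passing is Φ((true effect − 0.4)/standard error):

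| True effect size | 150 per arm | 50 per group |
|---|---|---|
| 0.40 | Φ(0) = 50% | Φ(0) = 50% |
| 0.556 | Φ(1.35) = 91% | Φ(0.78) = 78% |

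The 50% does not change with sample size. At 150 per arm, an 80% chance of passing needs a true effect size of 0.4 + 0.842 × 0.1155 = 0.50.

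**The case against.** The sample-size calculation itself is not wrong. The beta of 20% comes straight after 5 points and SD 9, and those inputs give the stated number. The defect lies in how the target is labelled and in what is left unstated.

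A reader might infer that the trial has only 51% power for the 0.4 on which success is judged. The protocol does not support that. The 51% belongs to 50 per group, meaning patients with MDI of at least 20, and even that cutpoint was later moved to 15. Sections 11.1 and 11.2 put the analysis on all included patients, where power for significance at 0.4 is 93%.

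A reader might also count a third minimal important difference in the 3 points and SD 7.5. That passage is marked as an example of the formula. The plan states two targets, not three.

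The two targets could have been meant for different populations: 5 points for patients with raised MDI, and a diluted 0.4 for everyone. That is possible, but section 11.1 does not say so and gives no separate SD for all patients. It is a reason to ask for clarification; it does not reconcile the figures.

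Finally, any observed-effect threshold is passed about half the time when the truth sits exactly on it, and requiring both significance and a minimum observed effect is a legitimate choice. This stands. The threshold is not an error, but its consequence at the effect named as minimally important should be stated.

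**Conclusion.** The point holds in this form. Section 11.1 names two minimal important differences that its own definition and SD make unequal: 0.4, and 0.56 (0.54 with the SD taken over both arms together). The 50 per group and the 80% power belong to the larger one, in the MDI subgroup. At 0.4 that subgroup would have about 51% power and would need about 100 per group. For the all-patient comparison that section 12 uses, the protocol states no power. It is about 93% for significance at a true 0.4, while the chance of meeting the observed-effect criterion is about 50%, rising to about 91% at a true 0.56.

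The other section 12 conditions, on PPS and on blood pressure and cholesterol, must also be met, so at a true 0.4 the chance of an overall positive conclusion cannot exceed that of the MDI criterion.

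The figures assume two-sided 5% tests, equal arms, complete data unless noted, and an unadjusted comparison of changes. The finding does not show that 300 patients are too few for significance, nor that the success threshold should move.

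**What to change.** In section 11.1:

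1. State which minimal important difference applies, to which population, and reconcile 0.4 with 5 points and SD 9. At SD 9, 0.4 is 3.6 points and 5 points is 0.56.
2. State that the 80% power refers to 5 points (effect size 0.56) in the MDI subgroup.
3. Add the power for the all-patient analysis: about 93% for significance at a true 0.4 with 150 per arm and complete data.
4. Disclose that the section 12 criterion of an observed effect size of at least 0.4 has about a 50% chance of being met at a true 0.4, and report the effect size with its 95% confidence interval.

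Keep the section 12 threshold as it is. Raising it to 0.56 would only move the 50% problem to a true 0.56, and replacing it by significance alone would loosen the criterion. Either would be a substantive change after data on the first 60 patients had been examined.

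The cost is an amendment to the text of section 11.1. No extra patients are needed. The downside is that the stated probability of success becomes less favourable.
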